## Sample size calculation

The sample size calculation of the present study was informed by data from a previous study [21] on psychological effects of high-intensity exercise, which showed a significant reduction in anxiety levels in 33 participants with anxiety disorders. We conducted a power calculation using https://clincalc.com/stats/samplesize.aspx. We assumed a baseline mean of 30 on the Beck Anxiety Inventory (BAI) for each group. The expected post-treatment BAI scores are 14 for the high-intensity group and 22 for the low-intensity group. With a significance level (alpha) of 0.05, SD of 7 and 80% power, the required sample size is 24. This means we need 12 participants per group to detect significant differences using a two-tailed *t*-test. Previous studies have found that the average attrition rate is 20% [33].

To account for an expected attrition rate of about 20% [33], the final target sample size is 30 participants (15 per group), representing the minimum required for adequate power. Additional participants may be included if recruitment permits, to further strengthen statistical power. Potential missing data will be addressed using linear mixed-model analyses, since this analysis is robust to missing-at-random mechanisms. Sensitivity analyses based on both intention-to-treat and per-protocol datasets will be applied to assess the robustness of the findings.

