### Statistical analysis

Data management and analyses are performed using SPSS 30 (SPSS Inc., Chicago, IL, USA). Data will be analysed using descriptive and inferential statistics. Continuous variables are presented with mean ± SD and 95% CIs.

The effect of the intervention will be assessed by examining change scores on the BAI and HADS (primary outcomes) and blood pressure and EKG (secondary outcomes). Changes from baseline to post-tests (immediately, after four weeks, and after three months) will be analysed.

Single measures (e.g. baseline data) will be analysed using ANOVA or linear regression, provided the statistical assumptions for linear models are met. Variables will be assessed for normality through visual inspection of histograms and Q-Q plots, along with a formal test for normality (Shapiro-Wilk test). If the assumption of normality is violated, non-parametric tests will be applied. ANOVA with repeated measures will be used to analyse changes in quantitative data (change scores) and to compare the two groups.

Missing data will be handled using linear mixed-model analyses, which provide unbiased estimates under the assumption that data are missing at random and allow inclusion of all available observations. Furthermore, multiple imputation will be applied as a sensitivity analysis to assess the robustness of the results to potential missingness.

We will also use Bonferroni corrected post hoc comparisons when performing multiple comparisons, ensuring that the overall significance level remains accurate. Additionally, effect sizes are estimated based on Cohen’s *d* (0.2 = small effect, 0.5 = medium effect, and 0.8 = large effect).

Participants with mild-to-moderate depressive symptoms will be eligible for inclusion, as anxiety and depression frequently co-occur in clinical populations. Due to our limited sample size, formal subgroup analyses based on depression status will not be conducted. Instead, the baseline depressive symptom scores (HADS-D) will be entered as a covariate in the statistical models to adjust for their potential influence on anxiety outcomes.

Age will be included as a covariate in all primary and secondary analyses. In addition, exploratory subgroup analyses will be performed by age group (< 40 years vs ≥ 40 years).

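### If the mixed model's response is change from baseline, as the text implies, its claimed protection against missing-at-random dropout is not secured when dropout differs by arm

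*Protocol article*

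**What the plan says.** Every statement about the treatment effect in the Statistical analysis section concerns change:

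- "The effect of the intervention will be assessed by examining change scores on the BAI and HADS"; blood pressure and EKG are treated the same way as secondary outcomes.
- "Changes from baseline to post-tests (immediately, after four weeks, and after three months) will be analysed".
- "ANOVA with repeated measures will be used to analyse changes in quantitative data (change scores) and to compare the two groups".

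The next paragraph turns to dropout and assigns it to linear mixed models. It describes these models as ones "which provide unbiased estimates under the assumption that data are missing at random and allow inclusion of all available observations". The Sample size calculation section repeats the assurance, choosing the mixed model "since this analysis is robust to missing-at-random mechanisms", and expects about 20% attrition. As a further check, "multiple imputation will be applied as a sensitivity analysis to assess the robustness of the results to potential missingness".

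The covariates named are baseline HADS-D and age. Baseline BAI, baseline HADS-A and baseline blood pressure are not named. The response variable of the mixed model is not stated.

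**The concern.** Missing at random allows dropout to depend on anything observed, including the baseline score of the outcome. A likelihood-based mixed model is protected against such dropout only if the observed baseline is in the model, either as one of the responses or as a covariate. A model whose response is post-test minus baseline, with no baseline covariate, has it in neither place.

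Two separate consequences follow. First, someone who leaves before the first post-test has no change score and is not in the analysis, although baseline BAI and HADS were recorded, so not all available observations are used. Second, the completers in an arm may start from a different baseline than everyone randomised to it. Because change is correlated with baseline, their mean change shifts. If the shift differs between arms, the contrast is biased.

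Unequal dropout is plausible here. Sessions differ sharply (a 4-minute hard bout with warm-up and cooldown, against 45 easy minutes), and the protocol itself hypothesises better adherence with high intensity.

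**Working it through.** **Inputs from the protocol (Sample size calculation).** Baseline BAI mean 30 in both arms; post-treatment means 14 (high intensity, HI) and 22 (low intensity, LI); SD 7; two-sided alpha 0.05; 80% power; 24 participants raised to 30 for about 20% attrition.

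**The plan's own figure.** n per arm = 2 × (1.960 + 0.842)² × 7² / 8² = 12.02, which agrees with the stated 12 by normal approximation. 24 / 0.80 = 30. About 0.20 × 30 = 6 participants are expected to be lost.

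**Assumptions not in the documents.** Pre-post correlation ρ = 0.3, 0.5 or 0.7; dropout before a single post-test, logistic in baseline BAI with log-odds 1 per SD where it depends on baseline; HADS-D correlated 0.5 with baseline BAI; no treatment-by-baseline interaction.

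**Formula.** Let B be baseline and Y = μ(arm) + ρ(B − 30) + error. The mean change among an arm's completers is μ(arm) − 30 − (1 − ρ) × s(arm), where s(arm) is the completers' mean baseline minus 30. The true contrast is (14 − 30) − (22 − 30) = −8, so

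bias of the change contrast = −(1 − ρ) × [s(HI) − s(LI)].

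By numerical integration with log-odds 1 per SD, s = −0.64 at 10% dropout, −1.21 at 20% and −1.77 at 30%. With log-odds −1 at 20% it is +1.21, and with no dependence it is 0.

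**Results, in BAI points at ρ = 0.3 / 0.5 / 0.7.** Positive means the HI benefit is understated. The HADS-D-adjusted column is from large-sample simulation.

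| Dropout pattern | s(HI) − s(LI) | Unadjusted bias | HADS-D-adjusted bias |
|---|---|---|---|
| Same dependence, 20% in each arm | 0 | 0 / 0 / 0 | 0 / 0 / 0 |
| Dependence in HI only, 20% in each arm | −1.21 | 0.85 / 0.61 / 0.36 | 0.64 / 0.46 / 0.28 |
| Same dependence, HI 30%, LI 10% | −1.13 | 0.79 / 0.57 / 0.34 | 0.60 / 0.43 / 0.26 |
| Same dependence, HI 10%, LI 30% | +1.13 | −0.79 / −0.57 / −0.34 | −0.60 / −0.43 / −0.26 |
| Opposite dependence, 20% in each arm | −2.43 | 1.70 / 1.21 / 0.73 | 1.31 / 0.94 / 0.56 |

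For example, dependence in HI only at ρ = 0.5 gives −(1 − 0.5) × (−1.21) = 0.61.

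**The same setting with baseline in the model.** In simulation at 15 per arm (no dependence; the same dependence at equal rates or with HI 30% and LI 10%; HI only; opposite), a likelihood analysis with baseline as a response gave contrasts between −7.95 and −8.03. In large samples at 20% dropout in each arm, change scores with baseline BAI as a covariate gave −7.99 to −8.03. The second analysis still excludes baseline-only participants, so their exclusion is not in itself what biases the contrast. The bias comes from not conditioning on baseline.

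**The case against.** The strongest reply is that the protocol never says the mixed model's response is change. The sentence that ties a method to change scores names repeated-measures ANOVA. A mixed model on raw scores, with change taken as a visit contrast, would also fit the wording and would have the properties claimed. This stands: a reader might infer that the protocol definitely commits to a change-score mixed model and that its claim is therefore false, but the text supports only an inference. It is still the natural reading, since change is the only analysed quantity named and the mixed model is introduced as the way to handle missing data in that analysis. Detailed model specification can be left to an analysis plan. The point survives because the article asserts properties that its stated quantity and covariates do not secure.

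A reader might also infer that any baseline-related dropout biases the comparison. It does not: in this setting, dropout alike in both arms leaves the contrast at −8. Bias needs a dropout rate or baseline dependence that differs by arm, or a treatment-by-baseline interaction.

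The planned safeguards count for something. HADS-D adjustment removes part of the bias (0.61 falls to 0.46 in the example). Multiple imputation can use the baselines of people without a post-test, but as a sensitivity analysis it does not make the statement about the mixed model true.

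Finally, the bias is small beside the noise. With 12 completers per arm the standard error of the unadjusted change contrast is 7 × √[2(1 − ρ)] × √(2/12), or 3.38, 2.86 and 2.21 at the three correlations. The adjusted one-arm bias is 0.13 to 0.19 of that and the opposite-dependence bias 0.25 to 0.39, so it would seldom decide the result alone.

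**Conclusion.** The concern holds in conditional form. If the mixed model analyses change from baseline with only HADS-D and age as covariates, it neither includes everyone with data nor is guaranteed unbiased under missing at random. With one-arm dependence or unequal dropout rates, the HADS-D-adjusted bias is about 0.3 to 0.65 BAI points; with opposite dependence it is about 0.6 to 1.3. That is roughly 3% to 16% of the planned 8 points (0.26/8 and 1.31/8).

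The direction depends on who leaves. Loss of more anxious participants mainly from the high-intensity arm understates its benefit. If the hypothesised adherence advantage of high intensity carries over to dropout, the same mechanism overstates the benefit, by 0.26 to 0.60 points in the 10% versus 30% case.

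The correlation, dropout slope, HADS-D correlation and arm-specific dropout are all assumed, and the sizes are for BAI at one post-test. The point is modest in size but worth correcting, because the mixed model is the plan's main protection against the attrition it expects.

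**What to change.** State the response of the mixed model. Fit it to the raw BAI and HADS scores at baseline and at the three post-tests (t1, t2, t3), with visit, arm-by-visit terms, a common baseline mean for the two arms and an unstructured covariance. Report the arm difference in change at each visit as a contrast from that model, and do the same for blood pressure. Every randomised participant with a baseline value then enters the likelihood, and the two stated properties hold given a correctly specified model.

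At minimum, if change stays as the response, add the outcome's own baseline value as a covariate. That removes the bias from baseline-related dropout but still excludes baseline-only participants, so the statement about including all observations would have to be withdrawn.

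The cost is a change of response variable in the syntax and a sentence of text. The baseline values are already collected, and SPSS mixed models can fit either version.

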## Abstract

**Background:**

This protocol was developed to describe the design of a randomised controlled trial that will examine the clinical efficacy of a 4-week comparison of high-intensity vs. low-intensity physical training for people suffering from anxiety. The hypothesis is that the high-intensity group will have greater benefit in terms of reduced anxiety symptoms, improved physical health (blood pressure) and better adherence.

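### The only missing-data sensitivity analysis is plain multiple imputation, which normally assumes missing at random just as the mixed model does, so their agreement says little about outcome-related dropout

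*Protocol article*

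**What the plan says.** The Statistical analysis section gives the main missing-data method and its condition: "Missing data will be handled using linear mixed-model analyses, which provide unbiased estimates under the assumption that data are missing at random". The next sentence adds the check: "multiple imputation will be applied as a sensitivity analysis to assess the robustness of the results to potential missingness". The Sample size calculation section repeats the basis ("Potential missing data will be addressed using linear mixed-model analyses, since this analysis is robust to missing-at-random mechanisms") and adds "Sensitivity analyses based on both intention-to-treat and per-protocol datasets will be applied to assess the robustness of the findings". It also plans for loss: "To account for an expected attrition rate of about 20% [33], the final target sample size is 30 participants", 15 per group.

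The Statistical analysis section names a second model for the group comparison: "ANOVA with repeated measures will be used to analyse changes in quantitative data (change scores) and to compare the two groups". Nowhere does the protocol state a delta adjustment, a reference-based or pattern-mixture analysis or a tipping point, and it names no auxiliary variables for the imputation.

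**The concern.** A sensitivity analysis for missing data is informative when it changes the assumption that the main analysis cannot verify. Here that assumption is missing at random. Unqualified multiple imputation ordinarily keeps it. The intention-to-treat and per-protocol datasets change who is analysed, not what is assumed about unseen scores.

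The protocol's own features make outcome-related loss plausible. About 20% attrition is expected, the primary outcomes are self-reported, and the Discussion accepts that participants know their training intensity. A serious medical incident leads to withdrawal from the study. Adherence is expected to differ by arm ("the high-intensity group will have greater benefit in terms of reduced anxiety symptoms, improved physical health (blood pressure) and better adherence"). If those who leave differ in unseen anxiety, and differ by arm, the estimated difference is biased. The planned check would tend to agree with the biased estimate.

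**Working it through.** **1. The plan's own figures.** The Sample size calculation section assumes BAI 14 versus 22 (difference 8), SD 7, two-sided alpha 0.05 and 80% power. Per arm: 2 × [7 × (1.960 + 0.842) / 8]² = 12.02, so about 24 in total. Inflated for 20% loss: 24 / 0.8 = 30, or 15 per arm. Shared equally, the expected loss is 3 per arm, 6 in all.

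**2. Why the two analyses agree.** Take a participant who leaves before the first post-treatment visit, so that only arm and baseline are known. The mixed model then estimates the arm difference from the regression of outcome on arm and baseline among those observed. Standard imputation draws the missing scores from that same fitted regression. Points that lie on average on the fitted line leave the line where it was. The two estimates therefore differ only by Monte Carlo noise, unless the imputation uses information that the mixed model does not.

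**3. Simulation with no true difference.** Assumed, not in the documents: correlation 0.5 between baseline and outcome, loss with weight exp(1.5 × standardised unseen outcome), so that poorer outcomes are likelier to be lost, and imputation from arm and baseline only. From the protocol: 15 per arm, SD 7, 6 of 30 lost. There were 2,000 trials per scenario, with a repeat run of 1,500.

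| Loss (high v low intensity) | Shared bias, BAI points | Bias / 8 | Rejection, mixed model / imputation |
|---|---|---|---|
| 3 v 3, same selection | about 0 (0.07) | 1% | 7.1% / – |
| 4 v 2 | 0.8 | 10% | 8.4% / 7.2% |
| 5 v 1 | 1.7 (1.6 in the repeat) | 21% | 11.2% / 10.3% |
| 6 v 0 | 2.5 | 31% | 16.8% / 15.1% |
| 3 v 3, opposite selection by arm | 2.6 | 33% | 19.5% / 17.9% |
| Random loss | – | – | 4.5% / 3.7% |

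Where agreement was tabulated, the two methods gave the same significance verdict in about 96% to 99% of trials, whether or not the estimate was biased.

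**4. Simulation with the planned 8-point effect.** 3 lost per arm, three post-treatment visits, correlation 0.5, 600 trials per scenario. Mean estimated difference:

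| Dropout | Complete data | Mixed model | Imputation |
|---|---|---|---|
| Random | -8.12 | -8.12 | -8.11 |
| High arm weighted to poor outcome | -8.00 | -9.20 | -9.19 |
| Worst 3 in high arm | -8.01 | -9.89 | -9.87 |
| Worst 3 in high arm, best 3 in low arm | -8.08 | -11.87 | -11.87 |

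The bias runs from 0 to 3.8 points. The mean gap between the methods is at most 0.03, and its correlation with the actual error is about 0 (-0.04 to 0.01).

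**5. Direction.** With a true 8-point effect and six poor-outcome losses all from the low-intensity arm, both methods understate the effect by 2.6 points. Rejection is 54.7% for the mixed model and 51.6% for imputation, and they agree in 95% of trials.

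**6. What a delta shift does.** Adding δ to imputed scores moves the difference by (m_H × δ_H − m_L × δ_L) / 15, where m is the number missing in each arm.
- 6 v 0 loss, δ = 7: 6 × 7 / 15 = 2.8, so -2.52 + 2.8 = 0.28 (simulated 0.27).
- Worst 3 in the high arm, δ = 5: 3 × 5 / 15 = 1.0, so -9.87 + 1.0 = -8.87 (simulated -8.87).
- 3 v 3 loss, equal δ in both arms: the shift is 0. Opposite-direction selection stays uncorrected (-2.63 simulated, against -2.64 without the shift).
- 3 v 3 loss, δ = 8: 1.6 points if applied in one arm, 3.2 if applied in opposite directions.

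**The case against.** Several points on the other side stand.

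- The text never says that the imputation assumes missing at random, and an imputation model is ordinary SAP content. True. But the protocol does name the method and its purpose, and nothing in it points to a departure from that assumption.
- Imputation has a proper use. Repeated-measures ANOVA normally drops incomplete cases, and imputation is a real check on that. This stands, but it does not test departure from missing at random.
- The near-identity depends on imputing from arm and baseline only. The trial also records completed sessions and heart-rate data. With an assumed auxiliary variable seen in dropouts and correlated 0.5 to 0.8 with the outcome, the 6-versus-0 imputation bias fell from about 2.5 to between 2.0 and 1.3, and its correlation with the primary estimate to between 0.96 and 0.91. The bias was reduced, not removed.
- Equal loss of 3 per arm, which the inflation implies, gives almost no bias if selection is alike in both arms. This limits the size of the concern, although nothing ensures like selection.
- The adherence hypothesis, if it carried over to dropout, points to more loss under low intensity, and so to bias against high intensity. With 1 v 5 or 0 v 6 loss and no true effect, false claims favouring high intensity occurred in 0.8% or 0.2% of trials. Adherence is also not the same as outcome missingness.

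A reader might infer that the plan will declare the result robust whenever imputation agrees with the mixed model. The protocol states no such rule.

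**Conclusion.** The point holds in a limited form. The one missing-data sensitivity analysis named does not, as stated, vary the assumption on which the main analysis depends, so agreement would be weak evidence against outcome-related dropout. Under the assumed selection, the shared bias runs from about 0 to 2.5 BAI points (up to 31% of the planned difference) as the split moves from 3 v 3 with like selection to 6 v 0. It can go either way, according to which arm loses more.

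It would be tempting to say that the trial faces a false-positive rate near 17%, or that imputation must reproduce the mixed-model result whatever happens. The documents support neither. The first needs 40% loss in one arm and none in the other, and the second needs an imputation without auxiliary variables. The selection form, its strength and the correlation of 0.5 are assumptions; the documents give none of them. This is a cheap improvement to the plan and does not invalidate the main analysis.

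**What to change.** In the Statistical analysis section:

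1. Keep the linear mixed model as the missing-at-random analysis.
2. Say that plain multiple imputation rests on the same assumption, and present it as a check on implementation or on a completers-only ANOVA.
3. Add delta-adjusted multiple imputation for BAI and HADS over a prespecified grid. For BAI, 0 to 8 points is an example; it is an assumed range that needs justifying in advance, and HADS needs a grid on its own scale.
4. Shift each arm separately, both arms together, and the arms in opposite directions. A common shift alone does nothing when losses are equal.
5. Report the tipping point, meaning the smallest shift that changes the conclusion, or state that it lies beyond the grid. As a rough guide, with an estimated difference of exactly 8 and 3 of 15 imputed in one arm, significance is lost at about (8 − 2.048 × 7 × √(2/15)) / 0.2 = 13.8 points. The range should therefore be set with the tipping point in view, and the plan should say beforehand which shifts count as plausible.

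The cost is a short addition to the text and a loop that adds a constant to imputed values before pooling. It needs no extra data or participants. The downside is that a positive result may be shown to be more fragile.

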## Methods/design

This is a study protocol for a randomised controlled trial designed to test the effects of high intensity training compared to low intensity training on anxiety levels.

There will be a random 1:1 allocation into two groups. The two groups are high intensity exercise (1 × 4 minutes performed two times per week with a heart rate of 85–95% of maximal heart rate, corresponding to ≥ 16 on the 6–20 Borg scale) and low intensity exercise (45 minutes performed two times per week with a heart rate of approximately 60% of maximal heart rate, corresponding to 9–11 on the 6–20 Borg scale) [26]. The high intensity group will perform a 10-minute warm-up prior to the high-intensity bout, and a 5-minute cooldown. Due to the low intensity in the low intensity group, a warm-up is not considered necessary.

The total amount of training sessions for both groups will be eight. The high intensity exercise group will serve as the intervention group, while the low intensity exercise group will serve as an active control group.

The trial will be conducted in accordance with the Standard Protocol Items: Recommendations for Interventional Trials statement (SPIRIT) [27].

The trial has been approved by the Data Protection Officer at the University Hospital of North Norway and the Regional Committee on Health Research Ethics (approval number 714458) and registered at ClinicalTrials.gov (Trial registration number NCT06881758).

Participants will provide written informed consent before allocation to the two intervention groups, and they will be randomised into a high-intensity training group and a low-intensity training group, following baseline measures.

Randomisation will be performed using counterbalanced block randomisation in a 1:1 ratio, stratified by sex, to ensure an equal distribution of males and females across the study groups. Block sizes of four–six participants will be used. This will allow for a balanced representation of both genders in each condition. Randomisation will be conducted using a computer-generated random number sequence via the website https://www.randomizer.org/.

Outcomes will be measured immediately after inclusion (baseline), right after the very last exercise session, four weeks after the last exercise session (primary endpoint) and three months after the termination of the intervention period (secondary endpoint) (Fig. 1).

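### Plain Bonferroni is valid for the multiple comparisons, but Holm's step-down version gives the same error control and is never less powerful; the size of the gain depends on a family and effect pattern that the protocol does not state

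*Protocol article*

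**What the plan says.** The protocol article's Statistical analysis section names one multiplicity method: "We will also use Bonferroni corrected post hoc comparisons when performing multiple comparisons, ensuring that the overall significance level remains accurate". It does not say which comparisons make up the family or how many there are. The same section lists BAI and HADS as primary outcomes and three post-baseline assessments: "Changes from baseline to post-tests (immediately, after four weeks, and after three months) will be analysed". Methods/design gives the later visits different standing: "four weeks after the last exercise session (primary endpoint) and three months after the termination of the intervention period (secondary endpoint".

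The trial is sized for one comparison of BAI. Sample size calculation states: "The expected post-treatment BAI scores are 14 for the high-intensity group and 22 for the low-intensity group", and then "With a significance level (alpha) of 0.05, SD of 7 and 80% power, the required sample size is 24". No effect is given for the other visits or for HADS, and no between-visit correlation is given.

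**The concern.** Bonferroni compares every p-value in a family of m with 0.05/m. Holm compares the smallest with 0.05/m, the next with 0.05/(m − 1), and so on, stopping at the first failure. Both hold the family-wise error rate at 5% or less whatever the dependence between tests. Holm's thresholds are never stricter, so it can only add rejections. For hypothesis testing, Bonferroni therefore has no advantage.

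This matters more in a small trial. The sample size calculation spends the full 0.05 on one contrast, so any corrected contrast starts below the planned power. Results at several visits, which bear on whether an effect lasts, are where a step-down method can help most.

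A smaller point is the wording. The sentence implies that the correction makes the overall level exact. Bonferroni gives an upper bound, and with positively correlated contrasts the actual level lies below 5%.

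**Working it through.** **Inputs from the protocol.** BAI difference 22 − 14 = 8 points, SD 7, two-sided alpha 0.05, 12 completers per arm, 15 per arm recruited (Sample size calculation); three post-baseline visits (Statistical analysis).

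**Inputs assumed.** A family of three between-group visit contrasts; the effect at each visit; SD 7 at each visit; a common between-visit correlation of 0.4 to 0.8.

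**1. The plan's own figure.** n per arm = 2 × SD² × (1.960 + 0.842)² / difference² = 2 × 49 × 7.849 / 64 = 12.02. This matches the stated 12 per arm to rounding. Power at 12 per arm is 79.9% by the normal approximation and 76.3% by the exact t-test. Attrition: 24 / 0.8 = 30, as stated.

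**2. Bonferroni with three contrasts.** The threshold is 0.05/3 = 0.0167. The noncentrality is (8/7) × √(12/2) = 2.80 and the critical t on 22 df is 2.59. Exact power per contrast is 58.8%. The normal approximation gives 65.7%.

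**3. Holm with the same three contrasts.** The thresholds are 0.0167, 0.025 and 0.05 on the ordered p-values. Power depends on the other contrasts, so it was simulated with pooled t-tests at 12 per arm, over correlations 0.4 to 0.8.

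| Assumed effects (points) | Contrast | Bonferroni | Holm | Gain (percentage points) |
|---|---|---|---|---|
| 8 / 8 / 8 | each visit | 59% | about 66–68% | about 8–9 |
| 8 / 6 / 4 | 8-point visit | 59% | 60–62% | 1–3 |
| 8 / 6 / 4 | 6-point visit | 33% | 39–40% | about 6 |
| 8 / 6 / 4 | 4-point visit | 14% | 21–24% | 7–10 |
| 8 / 0 / 0 | 8-point visit | 59% | 59% | about 0 |
| 8 / 8 (two contrasts) | each | 65–66% | 71–72% | about 5–6 |

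Power to reject at all three visits goes from 30–43% to 50–60% with equal effects, and from 7–12% to 16–23% with effects of 8/6/4.

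**4. At 15 per arm (no attrition), equal effects.** Power per contrast is about 72% with Bonferroni and 78–81% with Holm.

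**5. What does not change.** Holm's first step uses the Bonferroni threshold, so the chance of at least one rejection is identical (for example 81% for both at correlation 0.6 with equal effects). For the same reason the family-wise error under the global null is identical, at about 4–5% over these correlations. A single contrast tested alone at 0.05 is the same under either method.

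**The case against.** The strongest reply is that nothing here is wrong. Bonferroni is valid, prespecified and common, and the simulated family-wise error stays within 5%. That stands: the point concerns efficiency, and the remark on wording is minor.

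A reader might infer that the trial loses about 8 points of power at every visit for no return. The documents do not support that, for four reasons.
- No three-visit family is defined, and the 8-point difference is given only for post-treatment BAI. Equal effects at all visits is a favourable assumption. If the effect is confined to one visit, the gain there is about nil.
- The correction is attached to post hoc comparisons. If one visit on one scale is tested alone as primary, the choice of method does not touch it. If the post hoc comparisons are between time points, the contrasts simulated here are not the corrected ones.
- Bonferroni does give something in return: simple simultaneous intervals that match its tests, which Holm lacks. The plan promises 95% confidence intervals but does not say they are simultaneous or adjusted, so the loss is small but real.
- Most of the power shortfall comes from sizing the trial at an unadjusted 0.05. Holm recovers only part of it.

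It is also fair to say that the undefined family matters more than the method. So does the primary time point, which Methods/design places four weeks after the last session and Primary outcome measures describes as before the first and after the last session. Holm settles neither. The objections limit the size of the gain. They do not overturn the fact that Holm is never less powerful at the same error rate.

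**Conclusion.** The point holds as a cheap improvement, not as an error. For any family that is corrected, Holm keeps the same family-wise error control and can only add rejections. The gain ranges from about 0 to about 10 percentage points per contrast at 12 per arm, depending on an effect pattern and family that the protocol does not state. It is about 8–9 points for three equal 8-point effects and about 5–6 for two equal contrasts. If the effect fades, the gain falls mainly on the weaker visits. These figures assume t-tests on between-group visit contrasts, SD 7 throughout and correlation 0.4 to 0.8. They do not apply to the chance of at least one finding or to a single primary test, both of which are unchanged.

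**What to change.** In the Statistical analysis section, replace Bonferroni correction with *Holm (step-down Bonferroni) adjusted*. Replace the clause about the overall level with *controls the family-wise error rate at no more than 5%*. Report 95% confidence intervals, labelled as unadjusted, beside the Holm-adjusted p-values. List the comparisons in each corrected family in the same place, since neither method can be applied without that list.

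The cost is one sentence. No extra participants or data are needed, and the adjusted values come from ordering the unadjusted p-values from SPSS. The change should be made before any comparison by arm is seen, so that it cannot look result-driven. The small downside is that no simple simultaneous intervals match Holm, so an unadjusted interval may exclude zero beside a non-significant adjusted p-value. The labelling tells the reader why.
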